### Follow‐up

2.5

Follow‐up will be conducted at 1 month, and then every 1‐3 months following the ablation procedure with clinic visits. Patients will be scheduled examinations, including 12‐lead ECGs, 24 hour Holter recordings (3, 12, 24, and 36 months after the procedure), and/or ambulatory electrogram recorder (HCG‐801, OMRON Healthcare Co., Ltd). In patients with cardiac implantable electronic device, home monitoring will be adapted to facilitate the continuous monitoring of AF episodes. In patients without cardiac implantable electronic device, one‐channel electrocardiograms will be recorded twice daily for 1 year after the procedure except for the blanking period of the 90 days with the use of ambulatory electrogram recorder. Echocardiography and QoL questionnaires will also be obtained during the follow‐up (3, 12, 24, and 36 months after the procedure). LVEF will be recommended to be calculated during sinus rhythm. The QoL will be assessed by AFEQT questionnaires.^18^ All documented atrial tachyarrhythmias (ATs) lasting ≥30 seconds occurring outside the blanking period of 90 days will be considered as a recurrence. In the case of recurrences outside the after ablation blanking period, it will be recommended to perform a second catheter ablation. The sum of the durations of all episodes of ATs regardless of lasting ≥30 seconds or not, will be calculated and expressed as a percentage with respect to 24 hours to assess the AF burden in patients with cardiac implantable electronic device.

Adverse events (AE) will be collected during the study periods. An AE is defined as any untoward medical occurrence in a subject in this study, regardless of whether the causal relationship of the AE with the ablation procedure.

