### Sample size

2.9

The estimated sample size is 110 (55 in each group). The sample size was calculated based on the primary hypothesis. The recurrence rate of ATs after an ablation of AF has been reported to be comparable between the CB and RF ablation in patients without HF, ranging 65%‐90%,^11^, ^12^, ^19^, ^20^ and the recurrence rate of ATs after CB ablation in patients with HF with an LVEF ≤40% has been reported to be equal to those without HF.^21^ Therefore, we hypothesized that the incidence of recurrent ATs after an ablation procedure could be 20% in the AF patients from previous studies in both the CB and RF ablation groups. The sample size for the randomized comparison was calculated as 51 patients per group with a power of 80% by a two‐sided 95% confidence interval for the difference in the population proportions with a width that is equal to 0.35 when the two estimated group sample proportions are equally 0.20. To cope with a potential loss‐to‐follow‐up, a minimum of 55 patients per group will be enrolled in the study. Withdrawn patients will not be replaced.

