### Statistical analysis

2.12

Comparisons between the randomized groups will be performed on the basis of the intention‐to‐treat (ITT) principle. A per‐protocol basis analysis will also be performed to assess the robustness of the conclusions derived from the ITT basis analysis. The Kaplan‐Meier method will be used to estimate the survival curve, and the log‐rank test will be used to compare the curves between the groups for the time‐to‐event variables. Categorical variables will be analyzed using a chi‐square test or Fisher's exact test. Continuous variables will be presented as the mean ± standard deviation or median with the interquartile range (25th‐75th percentiles) and compared with the Student's t test or Wilcoxon rank‐sum test, as appropriate. A *P* value < .05 will be considered significant. Up‐to‐date versions of JMP (SAS institute) will be used to conduct analyses. The patient demographic data and outcome of catheter ablation in each group will be collected descriptively as presented in Tables 1 and 2.

**Table 1 joa312322-tbl-0001:** Patient characteristics at baseline

Age, years, n (%)
Male sex, n (%)
Height, cm
Weight, kg
NYHA functional class
History of a heart failure hospitalization
Number of heart failure hospitalizations
Blood pressure, mm Hg
Heart rate, /min
Duration of atrial fibrillation, months
Congestive heart failure, n (%)
Hypertension, n (%)
Diabetes mellitus, n (%)
Stroke and/or transient ischemic attack, n (%)
Structural heart disease, n (%)
Coronary artery disease
Valvular heat disease
Dilated cardiomyopathy
Hypertrophic cardiomyopathy
Others
Postopen heart surgery
CHADS_2_ score
CHA_2_DS_2_‐VASc score
Echocardiographic data
Left ventricular ejection fraction, %
Left atrial dimension, mm (%)
Left atrial dimension, <50 mm
Left atrial dimension, ≥50 mm
Computed tomography data
Pulmonary vein diameter, mm
Cardiac implantable electronic device
Pacemaker
ICD
CRT‐P
CRT‐D
History of anti‐arrhythmic drug use, n (%)
Disopyramide, n (%)
Cibenzoline, n (%)
Aprindine, n (%)
Pilsicainide, n (%)
Flecainide, n (%)
Propafenone, n (%)
Bepridil, n (%)
Sotalol, n (%)
Amiodarone, n (%)
Verapamil, n (%)
Beta‐blocker, n (%)
Digitalis, n (%)
Others, n (%)
Laboratory data

**Table 2 joa312322-tbl-0002:** The ablation procedure and complications

Procedure time (groin puncture to catheter extraction), min
Left atrial dwelling time
Fluoroscopic time, min
For cryoablation
Total freezing cycles, n
Total freezing time, s

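### The single-visit two-sample test named for change in LVEF and QoL leaves the interim readings and the baseline value unused at 3 years, which costs precision and can bias the comparison under some patterns of loss

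*Protocol article*

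**What the plan says.** Section 2.12 states how continuous variables are summarised and that they are "compared with the Student's t test or Wilcoxon rank"-sum test, as appropriate. It names no other method for a continuous outcome. The same section says "Comparisons between the randomized groups will be performed on the basis of the intention"-to-treat principle, with a per-protocol analysis for robustness, and sets the threshold as a P "value < .05 will be considered significant".

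Section 2.7.2 lists change and percentage change in LVEF and in QoL, at 1 and 3 years, among the key secondary endpoints. Section 2.5 says "Echocardiography and QoL questionnaires will also be obtained during the" follow-up, and gives the times: "3, 12, 24, and 36 months after the procedure). LVEF will be recommended to be calculated during sinus rhythm". QoL is measured with the AFEQT questionnaire.

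Section 2.9 sizes the trial on the primary endpoint only, with 55 per group after an allowance for loss, and adds: "Withdrawn patients will not be replaced". It gives no power, SD or loss rate for LVEF or AFEQT.

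**The concern.** A two-sample test on 36-month change compares one difference per patient, the 36-month reading minus baseline. The trial will already hold three intermediate readings on most patients, and the named test gives them no role. A patient measured at 3, 12 and 24 months but not at 36 has no 36-month change to enter. The baseline value enters only by subtraction, which is less efficient than using it as a covariate.

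Missing 3-year readings are foreseeable. Patients enter with LVEF of 40% or less, and death and heart-failure hospitalisation to 3 years are themselves endpoints. At stake is the precision of the 3-year CB v RF comparison of LVEF and quality of life and, under some patterns of loss, its accuracy. At 1 year only the 3-month reading goes unused, so the point is mainly about 3 years.

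**Working it through.** **1. The plan's own figure.** The article states 51 per group "with a width that is equal to 0.35 when the two estimated group sample proportions are equally 0.20". With a continuity correction the width is 2 × [1.96 × √(2 × 0.2 × 0.8 / n) + 1/n]. This gives 0.3536 at n = 50 and 0.3497 at n = 51, so 51 reproduces. Enrolling 55 allows for 4/55 = 7.3% loss. These figures concern the primary endpoint and give no power for LVEF or AFEQT.

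**2. What missing readings cost the planned test.** In units of the SD of change, the difference detectable with 80% power (two-sided 5%, normal approximation) is (1.96 + 0.842) × √(2/n). Power at 0.54 SD is Φ(0.54/√(2/n) − 1.96).

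| n per arm with a 36-month reading | Missing | Detectable difference | Power at 0.54 SD |
|---|---|---|---|
| 55 | 0% | 0.53 SD | 81% |
| 50 | 9% | 0.56 SD | 77% |
| 44 | 20% | 0.60 SD | 72% |
| 39 | 29% | 0.63 SD | 66% |

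**3. What the baseline covariate is worth.** Let ρ be the correlation between baseline and 36 months, with equal SD σ at both. The variance of change is 2(1 − ρ)σ². The variance after baseline adjustment is (1 − ρ²)σ². The gain in effective sample size is their ratio, 2/(1 + ρ):

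- ρ = 0.41 (0.8⁴): 2/1.41 = 1.42
- ρ = 0.66 (0.9⁴): 2/1.66 = 1.21
- ρ = 0.70: 2/1.70 = 1.18

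**4. What the interim readings add.** The inputs here are assumptions: 55 per arm, SD 10 points, baseline plus four visits, correlation falling by a factor of 0.8 or 0.9 per visit, 2,000 simulated trials per setting. The rows below have random loss and no true difference. Effective sample size is relative to the t test on change.

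| Correlation per visit | Missing at 36 months | All visits, no baseline adjustment | All visits with baseline adjustment |
|---|---|---|---|
| 0.8 | 10% | 1.05 | 1.45 |
| 0.8 | 20% | 1.14 | 1.52 |
| 0.8 | 30% | 1.21 | 1.56 |
| 0.9 | 10% | 1.06 | 1.27 |
| 0.9 | 20% | 1.13 | 1.31 |
| 0.9 | 30% | 1.16 | 1.37 |

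Over all settings, including equal correlation, the interim readings alone add 0-21% (mostly 3-14%). With baseline adjustment the gain is 14-56%. Step 3 explains most of the second figure.

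**5. Power.** With a true difference of 5 points, a visit correlation of about 0.75 and loss depending on the last reading, power of the t test v the all-visit model was 70% v 76% (16% missing), 66% v 74% (24%) and 55% v 71% (29%, stronger dependence). These are gains of 6, 8 and 16 points. A separate set of runs with 8-30% missing gave 7 to 17 points and a standard error 9-18% smaller. The range is not a bound. When the baseline to 36-month correlation is only 0.41, the gain is larger because baseline adjustment is worth more. For example, at 16% missing the t test averages 4.56 (SD 2.22) and the adjusted model 5.03 (SD 1.87), so Φ(4.56/2.22 − 1.96) = 54% against Φ(5.03/1.87 − 1.96) = 77%.

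**6. Bias of the t test on change (LVEF points).**

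- Random loss: about 0.
- Loss related to earlier readings in the same way in both arms, no true difference: about 0.
- The same loss with a true difference of 5: −0.2 to −0.7 in the decaying-correlation runs; estimates of 4.39-4.85 at a visit correlation of about 0.75; 4.9-5.0, essentially unbiased, in a further set of runs.
- Loss related to earlier decline in one arm only, no true difference: +0.3 to +1.8 in the decaying-correlation runs.
- Equal correlation between all visits: no material bias in any run.

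The all-visit likelihood estimate stayed within 0.12 of the truth in the decaying-correlation runs.

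**The case against.** The sentence in 2.12 is a generic rule for every continuous variable, procedure times included, softened by "as appropriate". It does not name LVEF or AFEQT. A two-sample test on change at a stated visit is a standard analysis of the endpoint as section 2.7.2 defines it, and preferring a repeated-measures model is a choice of efficiency. This is fair as to severity. It does not remove the point, because no other method is named for these endpoints and a better one is available at almost no cost.

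A reader might go further and infer that patients without a 3-year reading will be dropped, contradicting the intention-to-treat commitment. The documents do not support that. They say nothing about missing readings, a two-sample test can be run on imputed data, and an article commonly leaves such handling to the full protocol or analysis plan.

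A reader might also infer that the 3-year answer will be biased. That too goes beyond the evidence. Bias needs loss related to earlier readings together with a difference between arms in outcome or in that relation. The documents establish neither, and several sets of runs showed none.

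Two further objections stand. The power gain cannot all be credited to the interim visits, since much of it comes from baseline adjustment. And a mixed model treats readings after death as merely missing, so it does not settle how deaths should count.

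**Conclusion.** The point holds as one of precision, with bias only conditional. For the 3-year change in LVEF and AFEQT, the named test uses neither the 3-, 12- and 24-month readings nor the baseline value as a covariate. Under the assumed inputs the power forgone is about 6 to 17 percentage points, partly from baseline adjustment, and more if baseline and 36-month values are weakly correlated. Bias ranges from none to a modest amount; the largest value, 1.8 points on an assumed SD of 10, needs about 30% missing with loss tied to decline in one arm only. Every SD, correlation and loss rate is an assumption, because the documents give none for these endpoints. No calculation supports a material problem at 1 year. These are secondary endpoints, so this is a worthwhile improvement that leaves the primary conclusion unaffected.

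**What to change.** In section 2.12, make the main analysis of LVEF and AFEQT a mixed model for repeated measures on all scheduled readings (3, 12, 24 and 36 months), with arm, visit, arm-by-visit interaction, baseline value and LA-diameter group (<50 v ≥50 mm, the allocation factor in section 2.10). Take the CB v RF difference at 12 and 36 months from that model. Keep the t or Wilcoxon test as a supportive analysis, including for percentage change. Report the number of deaths and of missing readings per arm beside each result, and state that the model's estimate does not by itself account for death.

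The cost is one paragraph of wording and a little more programming, with no new visits, data or patients. The small downside is that the model assumes missingness is explained by the observed readings.

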### Study organization

2.13

The research group consists of investigators at multicenter in Japan and an independent data monitoring committee. All study investigators will have completed at least 50 procedures with each study technique (CB ablation and RF ablation) to be able to participate in this study.

### Ethics

2.14

The study is registered at the UMIN Clinical Trials Registry (UMIN Clinical Trials Registry UMIN000032433). The study is being conducted in accordance with the Declaration of Helsinki and the Ethical Guidelines for Clinical Studies issued by the Ministry of Health, Labour and Welfare, Japan. This study received approval from the institutional review board (IRB) of the National Cerebral and Cardiovascular Center, Japan (M29‐174, April 25, 2018), along with the IRBs of all participating institutions. All participants will provide written informed consent.

## RESULTS

3

The results of this study are currently under investigation.

## DISCUSSION

4

There are some debatable questions about catheter ablation of AF in patients with HF. These questions will be addressed by the CRABL‐HF study.

### Impact of the difference in the PVI area and durability between CB and RF ablation on the efficacy

4.1

Patients with HF have elevated filling pressures and larger PV ostia, and this means that a larger isolation area may be required in patients with both HF and AF.^23^, ^24^ Some studies have reported the efficacy of catheter ablation of AF in patients with HF with respect to the mortality, HF hospitalization, and LVEF; however, it is noted that the ablation strategies in almost all of those studies allowed for a substrate based ablation such as a posterior isolation in addition to the PVI.^5^, ^6^, ^7^, ^8^ Therefore, it is possible that a wider area of the PVI may increase the efficacy of the catheter ablation of AF in patients with HF, and the PVI area is reported to be wider in RF ablation than CB ablation.^25^

The PV antrum for the PVI in patients with HF may be more thickened compared to that in those without HF because patients with HF have atrial hypertrophy.^15^, ^16^ The transmural lesion creation by the PVI may be difficult in patients with HF and the importance of the PVI durability may be emphasized more in those patients. Regarding the PVI durability, the CB ablation has some advantages as compared to RF ablation.^26^, ^27^

### Impact of the difference in the procedure process and lesion creation between CB and RF ablation on the safety

4.2

It is notable that, despite advances in the catheter ablation technologies and increased operator experience year by year, AF ablation procedure‐related complications and mortality have been rather increasing.^13^, ^14^ The presence of HF is associated with increases in the mortality and procedural complications.^13^, ^14^ Therefore, we still should pursue a better technology for catheter ablation of AF in patients with HF even though catheter ablation of AF in patients with HF has been thought to be highly safe based on studies from highly experienced centers.^4^, ^5^, ^6^, ^7^, ^8^ Regarding the safety, Chun et al found that the risk of cardiac tamponade is lower in CB ablation of AF than RF ablation, although the total complication risk including phrenic nerve palsy is higher in CB ablation.

## CONCLUSIONS

5

The CRABL‐HF study will be conducted to compare the efficacy and safety of catheter ablation of AF between CB and RF ablation in patients with HF.
